**Methods:**

This study will be conducted in four HIV clinics in Ghana’s Central Region using a three-phase design.

Preparation Phase (Year 1): Use mixed methods, including nominal group techniques with 40–60 stakeholders (WLWH, healthcare providers, policymakers), to prioritize ISS and refine HOPE into HOPE 2.0 or HOPE-inG.

Implementation Phase (Years 2–3): Conduct a hybrid type 2 cluster-randomized controlled trial, comparing HOPE 2.0 + ISS (intervention group) versus HOPE 2.0 alone (control group). A total of 1,152 WLWH and 80 health providers will be enrolled.

Sustainment Phase (Years 3–5): Evaluate the long-term sustainment of HOPE 2.0 and ISS using quantitative and qualitative methods.

Primary outcomes include patient-level screening and treatment uptake (effectiveness) and provider-level implementation metrics (adoption, cost, fidelity, penetration and sustainability). Data sources include surveys, interviews, electronic tracking and fidelity checklists at multiple organizational levels. Cost analyses will employ micro-costing methods, and fidelity will be monitored through structured observations and log sheets.

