To address some of these challenges, our research team developed and tested a HOme-based self-sampling cervical cancer Prevention Education (HOPE) toolkit [23]. The HOPE toolkit consisted of HPV self-sampling, the 3R (Reframing, Reprioritizing, and Reforming) communication model [23–26] and patient navigator support. The current study is an extension of the HOPE initiative to promote cervical screening among women WLWH in Ghana (hereafter referred to as HOPE-inG or HOPE 2.0). HOPE-inG retains the three core components of the original HOPE intervention and introduces a fourth component: implementation support strategies (ISS), which we define as implementation strategies most relevant to implementation support, which is concerned with moving (implementation) research into (implementation) practice. ISS facilitate health system adoption and sustainment and function most directly within the implementation setting and at the interface between implementation and policymaking entities.

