### The HOPE intervention

The evidence-based intervention (EBI) for our study is HOPE’s three-component combination intervention: a cervical screening self-sampling kit, the 3R communication model, and patient navigator support.

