#### Evidence-based 3R communication model

The dimensions of the 3R communication model are reframing, reprioritizing, and reforming. Reframing is derived from health communication strategies [34, 35] that contrast the consequences of not screening and delayed treatment of precancerous lesions of the cervix (loss-framed appeals) with the benefits of early detection and treatment (gain-framed appeals). Reprioritizing prompts individuals to consider the relatively low cost of screening and treating precancerous lesions against the significantly higher cost of cancer treatment and possible loss of life. Reforming involves correcting misconceptions about self-sampling to promote positive attitudes toward screening and treatment. In Ghana, application of the 3R model within the HOPE toolkit significantly increased screening uptake and treatment compliance, achieving100% rates in the intervention group [36, 37].

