#### Design

We will conduct a hybrid type 2 cluster randomized controlled trial to simultaneously evaluate the effectiveness and implementation of HOPE 2.0 using bridging factor-focused ISS. HIV clinics at the four selected secondary-level facilities will be cluster randomized 1:1 in a two-arm trial. WLWH in the intervention group will receive HOPE 2.0 from providers trained and supported to implement HOPE 2.0 using ISS-focused training materials and per the implementation plan developed in the Preparation Phase. After this intensive 6 month implementation phase, technical and clinical support from the study team and clinical experts to the intervention sites will be withdrawn, after which the Sustainment Phase will begin

WLWH in the control group will also receive HOPE, from providers without ISS or an implementation plan (Table 2 and Fig. 2). At the end of this 6 months period of implementation, the study team will provide ISS materials to control group health facilities to co-implement with HOPE 2.0. There will be a similar Sustainment Phase for the control sites.

**Table 2 Tab2:** HOPE-inG baseline provider training in intervention vs control arms

	**Topic**	**Intervention Arm**	**Control Arm**
1	Epidemiology of cervical cancer (CC) in women with and without HIV	Yes	Yes
2	The WHO cervical cancer elimination agenda	Yes	Yes
3	The HOPE intervention: components and evidence	Yes	Yes
4	Cervical cancer screening strategies	Yes	Yes
5	Pre- and post cervical screening counselling	Yes	Yes
6	Psycho-social support for clients with positive cervical screening results and their immediate family	Yes	Yes
7	Awareness creation, record keeping and documentation	Yes	Yes
8	Research ethics: participant recruitment, study procedures and collecting, documenting and reporting data	Yes	Yes
9	Delivering the HOPE intervention in Ghana: Implementation research to practice	Yes	No
10	Who is supposed to do what, where and when? The HOPE 2.0 implementation plan	Yes	No
11	How will we deliver the intervention? Implementation support strategies for HOPE 2.0	Yes	No
12	What resources do we have for successful implementation? Additional tools, job aids, support and training for delivering HOPE 2.0	Yes	No

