#### Sample size estimation

The sample size is calculated based on implementation outcomes of health system adoption, cost, fidelity, penetration, and sustainability.*For power calculation*, we used Power (1 − β) = 0.8 and α = 0.05 and did not assume equal cluster sizes. The coefficient of variation (CV) of cluster sizes is set to 0.2, allowing for a large variability between clusters. Methods from Donner et al. [59] implemented in R for cluster RCTs were used.*For binary outcomes**,* e.g., adoption, we assumed 15% adoption in the control group based on previous study [23]. Table 3 shows the sample size needed to detect increases in implementation outcomes (e.g., adoption) in the intervention arm from 15% to 25–50% with 80% power. We expect to achieve an increase of at least 15%, to 30% or more, for outcomes such as adoption.*For continuous outcomes* such as sustainability/sustainment, we used estimated variance = 1 (standardized), and variance within clusters = 0.95 (assuming a large proportion of individual WLWH variability). For average cluster sizes (sampling frame per facility) ranging from 400 to 600 WLWH, we have greater than 80% power to detect differences in mean scores between the intervention and control arms as small as 1.4. We aim to recruit at least 1,152 patients (288 per site × 4 sites, inclusive of 20% attrition for a minimum sample size of 240 per site) Thus, the sample size for the Intervention Arm is *n* = 576 and Control Arm is *n* = 576.

**Table 3 Tab3:** Power and sample size calculation

Intervention Numeric	Control Numeric	Minimum Sample Size Per Site
0.25	0.15	504
0.30	0.15	240
0.35	0.15	142
0.40	0.15	94
0.45	0.15	67
0.50	0.15	50

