#### Control arm

Providers and clinic managers at control sites will receive baseline training on study implementation, but will not receive any ISS or implementation plan training (Table 2). They will, however, be required to follow Steps 2, 3, and 4 described in the intervention arm described above, except for patient navigator support.

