### Outcomes measures

The primary outcomes of interest in this type 2 hybrid trial are 1) the effectiveness of the HOPE 2.0 intervention in increasing uptake of cervical screening among WLWH, and 2) the adoption of HOPE 2.0 intervention at the facility level. Other outcomes, including cost, fidelity, penetration, and sustainability, will be assessed as secondary outcomes. Additionally, Proctor et al.’s [61] client (i.e., WLWH) health outcomes will also be assessed (Fig. 2).*Cervical screening uptake* is defined as the proportion of WLWH in each study arm that successfully complete the cervical screening process. In the intervention arm, completing the process requires the WLWH to present to the clinic, collect a self-test kit, collect a cervical sample, and submit the sample to the clinic for testing. In the control arm, completing the process requires the WLWH to present to the clinic and receive a pap smear/cervical sample collection from a provider. WLWH in either study arm who do not complete the entire process will not be considered as completing uptake. Uptake assessment will therefore be determined as proportion of WLWH with complete screening out of all women enrolled in each study arm.*Program Adoption* is defined as the decision of healthcare workers (i.e., providers and management) and patients (described as patient uptake) to commit to and use HOPE 2.0 and ISS adoption. Adoption will be measured at provider, management, and patient levels using a variety of data logs, surveys, and interviews.At the management level, we will assess (i) the number of ISS training sessions attended and (ii) the degree to which ISS components are used to support providers.At the provider level, we will assess (i) the number of ISS training sessions attended, (ii) the degree to which ISS components are used, and (iii) the number of implementation plan steps followed. Additionally, we will assess providers’ (i) implementation experience (i.e., resource availability, managerial support, and technical issues confronted); and (ii) operational experience (i.e., workload increase or decrease, flow of health facility communication, and any skills needed).*Implementation Cost* is defined as the total expenses (facility/provider and patient) for implementing HOPE 2.0. Cost will be assessed at the health facility level in both study arms. We will use a micro-costing approach to estimate the economic costs associated with each study arm. The direct measure method of micro-costing involves tracking resources used and enumerating unit costs for each resource to precisely estimate cumulative costs associated with each study arm [62]. Implementation cost will be measured at the health facility level and patient level, utilizing a variety of cost-tracking databases throughout the study period to itemize, quantify, and value resources.At the health facility level, a cost-tracking database will be used throughout the study period to itemize, quantify, and value resources. Costs at the facility level include (i) number of hours staff spent on HOPE 2.0 training; (ii) sampling materials, including kits and laboratory testing costs; (iii) recruitment (i.e., time spent identifying and contacting eligible women, advertising materials, participant incentives); (iv) HOPE 2.0 delivery (with and without ISS); and (v) treatment and biopsies.Cost to the patient will include tracking of participant out-of-pocket costs (e.g., transportation, childcare, phone data, time spent on HOPE 2.0 procedures). French et al.’s outpatient cost survey [63] (5 items) will be adapted to measure patient-level costs.Note: Time effort will be estimated using the hourly wages of WLWH and healthcare workers.*Fidelity* is the degree to which HOPE 2.0 and its ISS are implemented as planned.At the provider level, utilizing surveys, log sheets, and interviews, we will assess (i) the degree of adherence to HOPE 2.0/ISS protocols (Intervention) and HOPE 2.0 (Control) during implementation, (ii) the dose of the program delivered, and (iii) the quality of program delivery.At the management level, we will assess (i) adherence to ISS protocol (Intervention only) and (ii) overall management support for providers (both arms).We will utilize log sheets and interviews, as well as observations, and the Process Evaluation Checklist (PEC) [64] throughout to track the fidelity of implementation and overall project progress.*Program Penetration* for this proposal is the integration of HOPE 2.0/ISS within the HIV subsystem of study facility settings [61]. We will assess penetration outcomes at provider and management levels by determining the proportion of personnel who actually deliver on a HOPE 2.0 program task/role, out of the number trained or expected to deliver on that task/role.At the management level, we will utilize log sheets and interviews to measure the expected tasks or roles to be evaluated, which will be (i) the provision of technical support and (ii) facilitating a conducive HOPE 2.0 implementation climate for providers.At the provider level, we will utilize log sheets and interviews to measure the expected tasks to be evaluated, which are (i) screening and recruitment of eligible WLWH, (ii) delivery of HOPE 2.0 to enrolled WLWH, and (iii) follow-up on all testing outcomes and completion of required documentation for these tasks/roles.*Program Effectiveness* is defined as the impact of the ISS on 1) providers' self-efficacy in implementing HOPE 2.0, 2) WLWH screening uptake, and 3) treatment outcome. We will assess effectiveness outcomes at management, provider, and WLWH levels utilizing surveys, log sheets, and interviews.At the management level, we will assess (i) the frequency of support that management delivers to providers, (ii) management self-efficacy in supporting HOPE 2.0 implementation, and (iii) challenges in supporting HOPE 2.0 implementation at their facilities, utilizing log sheets and interviews.At the provider level, we will assess (i) self-efficacy for implementing HOPE, (ii) fidelity of HOPE 2.0 intervention delivery, (iii) number of WLWH screened and women with positive results who are treated, and (iv) the type, frequency, duration, and quality of service provided to patients (WLWH).At the WLWH level, we will assess the impact of HOPE 2.0 on patients’ (WLWH) screening uptake (i.e., service outcome) and receipt of screening results, patient satisfaction, and for women with positive screening results, clinical follow-up, and evaluation for, and receipt of CC treatment where appropriate (i.e., client outcomes). Assessment procedures: WLWH in both study arms will complete the screening and satisfaction outcome survey within one month of completing HOPE 2.0. Within one month of screening, providers will check the lab registry and will review the electronic medical record to confirm screening completion. Treatment compliance will be evaluated within 6 months of positive result notification. The screening and treatment completion outcomes will be binary (yes/no), test results (positive, negative, or inadequate), treatment follow-up (yes, no, or lost-to-follow-up), and patient satisfaction will be measured using a patient satisfaction survey [65].

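### The article disagrees with itself on what the control arm receives (patient navigators, self-sampling), so the two-arm contrast as written cannot be attributed to ISS alone

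*Protocol article*

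**What the plan says.** - **Stated contrast.** The Abstract gives it as "comparing HOPE 2.0 + ISS (intervention group) versus HOPE 2.0 alone (control group"). The Design section of the Implementation phase says "WLWH in the control group will also receive HOPE, from providers without ISS or an implementation plan". Table 2 separates the arms only on the training topics about implementation research, the plan, ISS and supporting tools.
- **What HOPE is.** The section on the HOPE intervention lists "a cervical screening self-sampling kit, the 3R communication model, and patient navigator support". The Background says "HOPE-inG retains the three core components of the original HOPE intervention and introduces a fourth component: implementation support strategies (ISS"), which makes ISS part of HOPE 2.0.
- **What control sites do.** The Control arm section requires Steps 2, 3 and 4 "described in the intervention arm described above, except for patient navigator support". In the Intervention arm section, Step 2 is recruitment and 3R messaging by clinicians, Step 3 is kit supply by clinicians or navigators, and Step 4 is follow-up of positive tests with navigator support.
- **How control uptake is counted.** The Outcomes measures section requires attendance and a Pap smear or cervical sample taken by a provider. The intervention arm must collect and return a self-test kit.
- **What is claimed.** The first primary outcome is "the effectiveness of the HOPE 2.0 intervention in increasing uptake of cervical screening among WLWH", and Aim 2 is worded similarly. The same Outcomes measures section defines Program Effectiveness as the effect of ISS on provider self-efficacy, screening uptake and treatment outcome.

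**The concern.** A two-arm trial estimates one thing: the combined effect of everything that differs between the arms. If navigators are absent from control, that combined effect includes navigation, and the article itself treats navigation as active. Its section on patient navigator support says that navigators' work in the earlier HOPE intervention raised uptake and screening rates and shortened diagnostic delays. A difference in uptake or treatment could then be credited to ISS when some or all of it came from navigators.

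The comparator is also unclear in a second respect. If control women self-sample, both arms receive HOPE's kit and messages. If their samples are taken by providers, the arms differ in sampling method as well. The meaning of the primary effectiveness result depends on which applies.

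**Working it through.** **1. What differs between arms under each reading.**

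| Reading | Uptake contrast | Treatment follow-up contrast |
|---|---|---|
| Abstract and Design govern: control has all of HOPE | ISS and plan | ISS and plan |
| Control arm section, literal: exception covers Steps 2 to 4 | ISS and plan + navigators at kit supply | ISS and plan + navigators |
| Control arm section, narrow: exception covers Step 4 only | ISS and plan | ISS and plan + navigators |
| Outcomes measures definition governs: control samples are provider-collected | ISS and plan + self-sampling, with navigators at kit supply unless the exception is narrow | ISS and plan + navigators |

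Only the first row supports attribution to ISS (with its plan) for both outcomes, and the Control arm section contradicts that row. The narrow reading supports it for uptake but not for treatment. The last row supports it for neither.

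**2. Why analysis cannot repair this.** Where navigators differ by arm,

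observed difference = effect of ISS and plan + effect of navigators + their interaction.

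Every intervention site has both and every control site has neither. Randomization therefore identifies only the sum.

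**3. HOPE against no HOPE.** If Steps 2 and 3 apply in control, both arms get 3R messages and kits. No arm is without HOPE, so the contrast is an increment over a partial or full HOPE background.

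**4. Scale, for illustration only.** The article gives no navigator effect, so the shares below are assumptions. The only planning difference is 15% to 30%, stated for outcomes such as adoption. Table 3 gives 240 per site for it. With two sites per arm, a two-sided 5% t test on 2 df, 80% power (noncentrality 5.653) and zero intracluster correlation:

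n per site = 5.653² × [0.30 × 0.70 + 0.15 × 0.85] / 0.15² / 2 = 31.96 × 0.3375 / 0.0225 / 2 = 239.7, which rounds up to 240.

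So the planned figure reproduces. At the same 2 × 240 = 480 per arm:

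| Assumed navigator share of 15 points | Part due to ISS and plan | Power for a difference of that size |
|---|---|---|
| 0% | 15.0 points | 80% |
| 25% | 11.25 points | 62% |
| 50% | 7.5 points | 39% |
| 75% | 3.75 points | 15% |

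The table shows how much the attribution could matter. It is not an estimate, and the defect does not depend on it.

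**The case against.** **The navigator exception may be narrow.** It can be read as attached to Step 4 only. Step 2 gives navigators no role, and in Step 3 clinicians can hand out kits. The Site selection section counts navigators among existing staff to be engaged, and the eligibility and recruitment sections include them without restriction by arm. The evidence on navigators also comes from the earlier intervention. This stands as a real ambiguity. It would spare the uptake contrast but not treatment outcome, which the article also ascribes to ISS.

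**A reader might infer that no contrast in the trial can estimate the effectiveness of HOPE 2.0.** The documents do not support that without qualification. The Background counts ISS as a component of HOPE 2.0, so the phrase can mean the ISS-containing package against HOPE, which is a between-arm comparison. If the provider-collected definition governs, the contrast moves closer to HOPE 2.0 against clinician sampling. The Implementation phase hypothesis simply compares intervention with control, which the trial does. What stands is conditional: if both arms receive kits and 3R messages, HOPE against no HOPE is not estimated.

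**A reader might also infer that control uptake will be too high for a 15-point gain.** The comparison would be of "we assumed 15% adoption in the control group based on previous study" with the 100% "rates in the intervention group" reported in the section on the 3R model. The 15% is labelled adoption, which has provider and management measures as well as patient uptake. The 100% comes from an earlier group given 3R within the HOPE toolkit, navigators included. The article projects no such rate for this control arm, so the inference fails.

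**Conclusion.** The point holds as an unresolved contradiction about the control arm, with a direct consequence for what may be concluded. As written, the arms differ in ISS with its plan and also in navigator support, and the control sampling method is stated in two incompatible ways. The comparison cannot carry a claim that ISS by itself changed uptake and treatment outcome. On the literal reading both outcomes are affected; on the narrow reading only treatment follow-up is, provided that control women self-sample. The claim about HOPE against no HOPE fails only if both arms receive kits and messages. No numerical bias can be given, because the article states no navigator effect.

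**What to change.** 1. Reconcile the Abstract, the Background, the section on the HOPE intervention, the Design section of the Implementation phase, the Intervention arm and Control arm procedures, and Outcomes measures. They should agree on whether control includes navigators (and at which steps) and whether control women self-sample. Which arrangement is right is for the sponsor to settle.
2. Use one definition of HOPE 2.0 throughout, stating whether ISS is part of it.
3. If navigators differ by arm, state the contrast everywhere as ISS and implementation plan plus patient navigation versus the control package actually delivered. Word Aim 2, the first primary outcome and Program Effectiveness as the effect of that combined package, and do not attribute differences to ISS alone.
4. Report uptake descriptively by arm.

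The cost is protocol wording and a narrower claim. No extra participants or data are needed. The Discussion places the study at the start of the Implementation Phase, so the correction can be made before results are known.

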#### Assessments

Program implementation assessments for HOPE 2.0 will be conducted at multiple organizational levels using mixed methods [60] (Table 3).

Multiple points of assessment allow us to determine the progression of implementation and outcomes at different organizational/policy levels. Surveys will be completed in person or online via Qualtrics platform links and/or QR codes sent by SMS and email. Healthcare workers and research assistants will help WLWH complete the in person and online surveys. The standard of post-trial care is provided to research participants through Cape Coast Teaching Hospital. No compensation is available to participants who suffer harm from trial participation.

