#### Evidence-based patient navigator support

Patient navigators, trained lay or volunteer health workers, play a vital role in improving equitable access to, and sustained use of HPVSS [37]. In Ghana, they routinely deliver health education and community-based services for various conditions, including breast cancer and HIV [44]. Within the HOPE intervention, patient navigators motivated WLWH, facilitated questionnaire completion, addressed participant questions, and ensured timely distribution and return of HPVSS kits. These activities enhanced service uptake, improved screening rates, and reduced diagnostic delays, consistent with findings from other LMICs [23, 45, 46].

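### Site staff whose service and screening counts are outcomes may help with the satisfaction survey and confirm screening, a risk of information bias that is clearest for satisfaction and lower for uptake

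*Protocol article*

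**What the plan says.** **Survey help.** The Assessments section says: "Healthcare workers and research assistants will help WLWH complete the in person and online surveys". It does not divide the work between the two groups by survey or by arm. One of the surveys concerned is described under Outcomes measures: "WLWH in both study arms will complete the screening and satisfaction outcome survey within one month of completing HOPE 2.0".

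**Confirmation of uptake.** Screening uptake is a primary outcome, scored as completed screenings over all women enrolled in the arm. Outcomes measures says: "Within one month of screening, providers will check the lab registry and will review the electronic medical record to confirm screening completion".

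**Assessment of the same staff.** Provider-level effectiveness outcomes in the same section include the "number of WLWH screened and women with positive results who are treated" and the quality of the service given to women.

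**What differs by arm.** Sites are randomized whole, two per arm (Randomization). Table 2 gives topics 9 to 12, on the implementation plan, the implementation support strategies (ISS) and additional job aids, to the intervention arm only. Control sites follow the same delivery steps "except for patient navigator support" (Control arm).

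**The concern.** Site staff receive arm-specific training and support, so they can hardly be unaware of their arm, although the article does not mention blinding. In such a trial, protection against information bias comes largely from who collects the outcome and by what rule. Here two collection rules place site staff on both sides of the measurement.

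- **Satisfaction.** A woman may rate her care with help from a member of the team that gave it. Such answers tend to be more favourable.
- **Uptake.** Providers who are assessed on the number screened confirm who was screened. The check is timed from screening, a date that exists only for women already known to have screened. The denominator is everyone enrolled, so a completed screen that nobody follows up counts as no uptake.

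Error of equal size in both arms would not create a false difference. Error that differs by arm would. With two sites per arm, a difference between sites in survey help or record checking cannot be told apart from the effect of ISS.

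**Working it through.** The plan states no figure for misclassification or for agreement between sources, so there is nothing to reproduce. The check sets the passages side by side and then shows how the size depends on assumed error.

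**1. Is the same group on both sides?**
- Survey helpers: healthcare workers and research assistants (Assessments).
- Confirmation of screening: providers (Outcomes measures).
- Assessed on number screened and service quality: providers (Outcomes measures).
- Site selection uses one term, healthcare providers, for administrators, clinicians and support staff including navigators.

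The groups overlap, and no stated rule separates delivery from data collection.

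**2. Does the timing of the check fit the denominator?** The check runs within one month of screening, but the proportion is taken over all women enrolled. The text shown gives no dated check for an enrolled woman not known to have screened. Figures 2 and 4, which hold the time points and schedule, are not visible, so a fixed check may exist there.

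**3. Could the error differ by arm?** ISS, the plan and navigator support go to intervention sites only. Follow-up of test results and completion of documentation are themselves measured as a penetration outcome, so the protocol treats them as behaviour the programme may change. On the other side, Table 2 gives both arms topics 7 and 8, on record keeping and on collecting and reporting data. A difference is plausible but not shown.

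**4. What size would follow for uptake?** All error rates below are assumptions. The 15% and 30% are the values in Sample size estimation, given there for outcomes such as adoption.

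*Missed screens.* Observed rate = p × s, where p is true uptake and s the share of completed screens that are confirmed. Take s = 98% in the intervention arm and the same p in both arms.
- p = 30%, control s = 90%: 29.4% − 27.0% = 2.4 points.
- p = 30%, control s = 80%: 29.4% − 24.0% = 5.4 points.
- p = 15%, control s = 90%: 14.7% − 13.5% = 1.2 points.
- p = 15%, control s = 80%: 14.7% − 12.0% = 2.7 points.

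*False confirmation.* Observed rate = p + (1 − p) × f, where f is the share of unscreened women wrongly confirmed. Take p = 15% in both arms and f above zero in the intervention arm only. The spurious difference is then 0.85 × f.
- f = 2%: 1.7 points.
- f = 5%: 4.25 points.
- f = 10%: 8.5 points.

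*Equal error.* With f = 5% in both arms, a true difference of zero stays at zero. A true 30% versus 15% becomes 0.95 × 15 = 14.25 points, a slight dilution.

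For scale, the article plans on a 15-point difference. The illustrations run from 1.2 to 8.5 points, but the documents fix neither the mechanism nor the direction nor the rate. For satisfaction they give no figure from which a size could be derived.

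**The case against.** The strongest reply is that uptake is a yes/no fact checked against two records, both arms are trained in record keeping, and a screening survey and log sheets give further sources. Satisfaction is neither a primary outcome nor among the named secondary outcomes. An article also condenses data-collection procedures. Much of this stands: it lowers the risk for uptake and limits what rests on satisfaction. It does not dispose of the point, because the two rules are stated, not omitted, and the records are still checked by providers on a timetable that starts at screening.

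Four stronger readings are tempting and are not supported:

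- *That a navigator sits beside intervention women as they answer.* The statement that "patient navigators motivated WLWH, facilitated questionnaire completion" describes the earlier HOPE intervention. The Assessments section does not name navigators as survey helpers. HOPE-inG retains navigator support as a component, so a different pool of helpers by arm is a fair inference, but no more.
- *That intervention sites have more staff.* No passage says so. The Preparation phase surveys 10 providers from each site, and navigators are recruited without an arm restriction. What the control arm lacks is navigator support.
- *That the data are biased by a known number of points.* The rates above are assumptions, and only the part of the error that differs by arm matters.
- *That moving the tasks removes the problem.* Site staff would still create the source records, and women would still know what service they received.

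**Conclusion.** The point holds as a risk of information bias, not as demonstrated bias. It is clearest for satisfaction, where staff of the service being rated may help with the answers. It is lower for uptake, which is checked against the laboratory registry and the medical record. It distorts the comparison only if the error differs by arm. That is plausible, given what only the intervention sites receive, and could not be separated from the arm effect with two sites per arm. The documents neither show nor exclude it.

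The size is unknown; the illustrated 1.2 to 8.5 points for uptake rest wholly on assumed error rates. The conclusion also assumes that site staff know their arm, which follows from the arm-specific training but is not stated. It is a cheap improvement worth making, and nothing here shows that the trial's result would be wrong without it.

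**What to change.** - **Assessments.** Have the research assistants already named there, not site healthcare workers, help women with the satisfaction survey in both arms, by the same procedure.
- **Outcomes measures.** Replace "providers will check the lab registry and will review the electronic medical record to confirm screening completion" as the basis for scoring. Have the study research coordinators, who already take consent (Recruitment), match every enrolled woman against both the laboratory registry and the electronic medical record. Do this at one fixed time from enrolment, named in the plan and identical in both arms, and score uptake from that match. Keep both sources: the stated control-arm definition includes samples taken by a provider, so matching to the laboratory registry alone could itself capture the arms unequally.

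The cost is somewhat more research-staff time, for survey help to up to 1,152 women and a record match at each of four sites. The number of research assistants is not given, so the load should be checked. The change reduces the risk but does not remove it.

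A separate matter is untouched by this change. The Control arm section has control sites follow the self-sampling steps, whereas Outcomes measures defines control-arm completion as a Pap smear or provider-collected sample. Those passages must be reconciled.
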